### 2.6. Primary Outcomes—Motor Aspects

1. Activities of daily living (Section 2) and motor symptoms (Section 3)—Unified Parkinson's Disease Rating Scale (UPDRS)  The UPDRS scale has 4 sections, and in this study only Section 2 and Section 3 will be used, in order to measure the progression of the disease through the participants self-report. Each item is scored from 0 to 4 points, with the higher and lower values corresponding to greater and less disease severity, respectively [29].

### 2.7. Secondary Outcomes—Motor Aspects

1. Lower limbs' strength and power using the five times sit to stand test (5xSTST).  This test assesses functional mobility, dynamic strength, and muscle endurance of the lower limbs [30]. The execution consists of the participant sitting and rising from a chair, without arm support, as rapidly as possible for five times [30].2. Lower limb isometric muscle strength—Lafayette  The quantitative assessment of isometric muscle strength will be performed using a portable dynamometer (Lafayette manual muscle testing system model-01165), which will provide data for peak strength, average strength, and time to peak force. The abductor muscles, hip adductors and flexors, and knee extensors will be assessed [31].3. Dynamic balance and risk of fall—timed up and go test (TUG)  The TUG is used to determine mobility and the risk of fall by varying dual cognitive and motor tasks. All three test modes will be performed at the regular speed, in a comfortable and safe manner [32].4. Static and dynamic balance—mini best test  The balance evaluation systems test (BESTest), abbreviated as Mini BESTest, will be used to assess changes in static and dynamic postural balance. The test simulates daily activities and retrieves sensory information in some tasks in order to challenge balance [33].

### 2.8. Secondary Outcomes—Nonmotor Aspects

1. Sleep quality—*Parkinson's Disease Sleep Scale* (PDSS)  The PDSS is a *visual* scale that is used to identify nightly manifestations that may have interfered with sleep in the past week [5].2. Depressive symptoms—*Geriatric Depression Scale 15* (GDS-15)  This scale *assesses* nonsomatic symptoms of depression, such as psychological aspects and social implications [34].3. Quality of life—*Parkinson's Disease Questionnaire 39 (PDQ-39)*  This instrument *assesses*self-rated quality of life in relation to the previous month, using 39 questions grouped into eight dimensions: mobility, activities of daily living, physical discomfort, communication, emotional well-being, cognition, and stigma regarding PD [23].

### 2.9. Secondary Outcomes—Aquatic Motor Skills

1. Aquatic motor skills—Aquatic Functional Assessment Scale (AFAS)  The AFAS quantifies the quality of learning for aquatic motor and functional skills, divided into 26 motor behaviors based on motor mastery and independence in water [35, 36].

#### 2.9.1. Medication

All assessments and interventions will be carried out in the “on” period of dopaminergic medication. Any change in the medication prescription will be informed and considered grounds for exclusion from the research.

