### 2.2. Participants

Individuals with a clinical diagnosis of PD and classified in Stages 1–4 of the Modified Hoehn and Yahr (HY) Scale, residing in the city of Curitiba (PR), of both sexes, and vaccinated against COVID-19 will be invited to participate in the study, with consent to participate in the study voluntarily and sign the free and informed consent term (FICF).

The exclusion criteria will include cognitive, visual, and auditory impairments, as well as the use of wheelchairs (whether due to or not due to PD), cardiovascular surgery, or decompensated cardiac diseases that place the participant at risk, or any absolute contraindication to attend a heated swimming pool, and changes in dosages or parameters of the medication associated with PD during the course of the study [22, 23].

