### 2.5. Primary Outcomes—Cardiorespiratory Aspects

1. Cardiorespiratory performance—6-minute walking test (6-MWT)  The 6-MWT is a submaximal test used to indirectly measure cardiorespiratory fitness, functional capacity to exercise, walking distance, and walking observation, and it is a predictor of morbidity and mortality [24]. The incentive phrases and the full test will be conducted according to the guidelines for the 6-MWT of the American Thoracic Society [24].2. Heart rate variability (HRV)—Heart rate sensor  The HRV will be collected using a Polar H10 heart rate sensor, which will be placed slightly below the xiphoid process. The participant will remain lying down, quietly, in dorsal decubitus position for 10 min, with spontaneous breathing. The data will be exported in txt format to the *Kubios HRV Standard* 3.4.2 software, where ectopic beats, signs of artifacts, and sinus beats with less than 95% will be excluded from the study [25].  For the analysis in the time domain, the SDNN values, resulting from the standard deviation of all normal R-R intervals, representing sympathetic and vagal modulation, and the RMSSD, corresponding to vagal modulation, will be obtained by the square root of the mean square of the differences between adjacent normal R-R ranges minus one. The frequency domain is composed of the high frequency (HF), which indicates the activity of the vagus nerve on the heart, the low frequency (LF), which represents both the vagal and sympathetic components on the heart, with predominance of the sympathethic, and the LF/HF ratio that characterizes the sympathovagal balance [26, 27].3. Pulmonary volumes and capacities—spirometry  The examination of forced vital capacity (FVC), forced expiratory volume in 1 s (FEV-1), Tiffeneau–Pinelli Index (VEF1/FVC ratio) and maximal voluntary ventilation (MVV) will be performed using a portable spirometer.4. Maximal inspiratory pressure and maximal expiratory pressure—manuvacuometer  The maximal inspiratory pressure (MIP) and maximal expiratory pressure (MEP) are correlates of respiratory muscle strength (inspiration: diaphragm and intercostal muscles; expiration: abdominal muscles) and are measured in centimeters of water (cmH_2_0) using manovacuometry [28].

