#### 2.9.2. Allocation

The allocation will be carried out randomly with support from the Sealed Envelope website (https://www.sealedenvelope.com/simple-randomiser/v1/lists). The subjects will be divided into an intervention group and a control group for a 12-week period. Following this period, participants in the control group will have the opportunity to participate in the WPEP.

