#### 2.9.6. Sample Size

Based on the prevalence of individuals with PD in Curitiba, a sample calculation was performed using GPower 3.1. As a result, a sample of 30 individuals will be required, with 15 assigned to the intervention group and 15 assigned to the control group.

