### 2.10. Statistical Analysis

The data will be analyzed for sphericity and homogeneity with Shapiro–Wilk test. The ANOVA mixed model will be used to compare pre- and postintervention and intergroup comparisons. Afterward, a Bonferroni post hoc analysis will be performed on variables with statistically significant differences to identify which assessments differ from each other. The statistical power will be *p* > 0.05, and the effect size will also be shown. SPSS 20.0 statistical software will be used in all the analyses.

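### A change in PD medication after randomisation is grounds for exclusion from the research, which can bias the randomised comparison and shrink a trial of 15 per arm

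*Protocol article*

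**What the plan says.** Two sections of the protocol article state the rule. Section 2.2 (Participants) includes among the exclusion criteria "changes in dosages or parameters of the medication associated with PD during the course of the study". Section 2.9.1 (Medication), after requiring assessments and sessions to take place in the on period of dopaminergic medication, adds: "Any change in the medication prescription will be informed and considered grounds for exclusion from the research".

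Section 2.9.2 (Allocation) states that "The allocation will be carried out randomly with support from the Sealed Envelope website", with two groups for 12 weeks. Section 2.4 places one assessment before that period, one after it, and a third after 4 further weeks. Section 2.6 makes UPDRS Sections 2 and 3 a primary outcome and describes them as measuring disease progression. Section 2.9.6 gives the size: "a sample of 30 individuals will be required, with 15 assigned to the intervention group and 15 assigned to the control group".

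For the analysis, Section 2.10 states that "The ANOVA mixed model will be used to compare pre- and postintervention and intergroup comparisons". The article does not say that a participant excluded for a medication change is still assessed, or is still analysed in the allocated group.

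**The concern.** A criterion that can only be met during the study cannot screen people at entry. It acts on participants who have already been randomised, and its trigger may be connected with what the trial measures. Someone whose motor symptoms or daily activities get worse may have the prescription changed, and so may someone who improves. The two arms also know their allocation: one attends the pool programme, while the other is told to keep usual activities and avoid high-intensity exercise. Requests for a change, or willingness to make one, could therefore differ by arm.

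If people leave for reasons tied to arm and outcome, those who remain are no longer the groups that randomisation formed. The estimated effect on the UPDRS, and on other outcomes that move with medication, could be too small or too large, and the data could not show which. A larger sample would restore precision but would not remove the bias. Exclusion from the research also most naturally means that the later assessments are not made, and no analysis plan can recover data that were never collected.

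**Working it through.** **1. When the rule acts.** Section 2.2 times the event as during the study, Section 2.9.2 randomises at the start, and Section 2.4 runs 12 weeks plus 4 weeks of follow-up. The rule can therefore remove randomised participants at any point in up to 16 weeks.

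**2. The plan's own figure.** The total of 30 cannot be reproduced. Its stated basis is "Based on the prevalence of individuals with PD in Curitiba, a sample calculation was performed using GPower 3.1", with no effect size, SD or power. Section 2.10 offers "The statistical power will be *p* > 0.05, and the effect size will also be shown", which is not a usable power or significance level. The figures below therefore assume a two-sided 5% level and 80% power.

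**3. Shift in the difference.** Assume normally distributed change scores with SD 1, and let the worst fraction q of an arm be removed. The mean of those who remain improves by φ(z_q)/(1 − q), where z_q cuts off an upper tail of q. The article gives no rates, so these are assumed:

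| q | z_q | φ(z_q) | φ(z_q)/(1 − q) |
|---|---|---|---|
| 7% | 1.476 | 0.134 | 0.144 |
| 10% | 1.282 | 0.175 | 0.195 |
| 20% | 0.842 | 0.280 | 0.350 |
| 30% | 0.524 | 0.348 | 0.497 |

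- Controls 20%, exercise arm 7%: 0.350 − 0.144 = 0.206 SD. If the selecting variable correlates only 0.5 with outcome, 0.5 × 0.206 = 0.103 SD.
- Controls 30%, exercise arm 10%: 0.497 − 0.195 = 0.302 SD. At correlation 0.5, 0.151 SD.
- Nobody changes medication: 0.

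With the rates as shown, the shift hides a benefit. If they are swapped between the arms, its sign reverses.

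**4. What unequal rates imply.** If both arms share one worsening cut-off, 20% against 7% requires a true effect of 1.476 − 0.842 = 0.634 SD, and 30% against 10% requires 1.282 − 0.524 = 0.757 SD (unrounded z-values). Otherwise, prescribing must differ by arm.

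**5. A second model: one common cut-off in both arms.** Take a true effect of 0.8 SD and a cut-off that excludes 20% of controls. It lies 0.842 + 0.8 = 1.642 SD above the exercise-arm mean, so 5.0% of that arm is excluded. The observed difference is 0.8 − 0.350 + 0.109 = 0.56 SD. By simulation, excluding 10% or 30% of controls gives 0.65 or 0.49 SD. With no true effect and the same cut-off, the difference stays at 0.

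**6. Loss of precision (two-sample t-test, assumptions of step 2).**

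| Analysed | Detectable difference | Power at 1.06 SD |
|---|---|---|
| 15 + 15 | 1.06 SD | 80% |
| 12 + 14 | 1.15 SD | 73% |
| 12 + 12 | 1.20 SD | 70% |

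The 12 + 14 row matches the 20%/7% scenario: 0.20 × 15 = 3 and 0.07 × 15 ≈ 1 lost. The 12 + 12 row is a separate case, 20% lost from each arm. The planned analysis is a mixed ANOVA on repeated measures, so the table shows the relative cost of losing people. It does not give the trial's actual detectable effects.

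**The case against.** The strongest reply is that the bias is inferred. The article does not say why or how often prescriptions would change, or that the arms would differ. Few changes may occur in 12 to 16 weeks, and with no true effect and one rule for both arms the bias is nil. This stands as far as size and direction go. It does not rescue the rule, whose effect is harmless only if those conditions hold, and nothing in the plan makes them hold.

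A second reply is that the analysis population may be defined in a fuller document. That is fair: its absence from an article is no fault, and whether data already collected would be discarded is not stated. The point rests on the rule that is stated, which most naturally means withdrawal and loss of later assessments.

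A third is that stable medication isolates the exercise effect. That is a legitimate interest, but removing people after allocation does not secure it without risking the randomised comparison. A sensitivity analysis keeps that view available.

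Two stronger readings are tempting and are not supported:

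- A reader might infer from the word any in Section 2.9.1 that a change to any drug, not only PD drugs, leads to exclusion. The sentence before it concerns dopaminergic medication, and Section 2.2 limits the rule to PD medication. The two wordings differ and need reconciling, but a wider exclusion is not established.
- A reader might infer that Section 2.5 also removes participants, for a poor heart-rate trace. Its words are "ectopic beats, signs of artifacts, and sinus beats with less than 95% will be excluded from the study". The subject is beats and artifacts, in a passage on processing the recording, so this is loosely worded data cleaning.

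**Conclusion.** The point holds in this form: Sections 2.2 and 2.9.1 exclude randomised participants on a post-allocation event that may be related to outcome or to arm. Followed as written, this can bias the comparison on the primary outcomes in a direction that cannot be known, and it reduces a sample of exactly 15 per arm.

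That the rule acts after randomisation is certain from the text. The size is not. A shift of about 0.1 to 0.3 SD rests on assumed exclusion rates, normal change scores, and selection of the worst outcomes with correlation 0.5 to 1. It falls to zero if no one changes medication, or if both arms face the same rule and there is no true effect. A reader might infer that the comparison is certainly broken, or certainly biased toward no effect; the documents support neither.

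It should be settled before participants are excluded under the rule, because assessments not made cannot be recovered.

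**What to change.** In Sections 2.2 and 2.9.1, replace the exclusion with these provisions:

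- A change in PD medication after allocation is recorded, with its date and nature.
- The participant continues with the assessments already planned in Section 2.4.
- All randomised participants are analysed in their allocated arm, whatever the change.
- The analysis without those who changed medication is reported as a sensitivity analysis only.

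Reconcile the wording of the two sections, so that both name the same medication as the event to be recorded. No new entry criterion is needed to remove this source of bias. How medication itself is managed remains a clinical matter on which this point takes no view.

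The cost is a change of wording and visits that are already scheduled. The one downside is that the estimated effect then includes any medication changes made along the way, and the report should say so. Recruiting more people while keeping the exclusion is not an equivalent repair. To keep 30 evaluable at an assumed 20% loss would need 30/0.8 = 37.5, so 38 participants, and the possible bias would remain.

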#### 2.9.2. Allocation

The allocation will be carried out randomly with support from the Sealed Envelope website (https://www.sealedenvelope.com/simple-randomiser/v1/lists). The subjects will be divided into an intervention group and a control group for a 12-week period. Following this period, participants in the control group will have the opportunity to participate in the WPEP.

#### 2.9.3. Intervention Group

##### 2.9.3.1. WPEP

Individuals will participate in the WPEP at the Ana Carolina Moura Xavier Rehabilitation Hospital—Laborer Hospital Complex (CHT-HR), in groups of up to five participants, two times a week, with an approximate duration of 35 min, for 12 weeks, with a period of 48–72 h between training sessions, for muscle recovery, totaling 24 sessions.

The program will be divided into 10 min of warm-up, 15 min of HIIT, and 10 min of cool-down using the Ai-Chi method. Participants will be encouraged to maintain subjective perception of effort above seven on the Borg scale 0–10 [6, 11, 37–40]. In addition, every 4 weeks, the WPEP will assess the progression of the exercises in relation to the load, and every week the intensity, degree of difficulty, and independence in water will be assessed [6, 11, 37–40].  Table 1 shows the exercises that will be used in the WPEP.

The warm-up exercises will be performed at moderate intensity with the main purpose of joint warm up, increase in the heart rate, and social interaction between participants [6, 37, 39, 40]. The main part of the WPEP will consist of HIIT, with multiarticular physical exercises and large muscle groups will be performed [6, 37, 39]. The Borg scale 0–10 will be used to monitor and ensure that the exercises are performed at the intended intensity target [6, 38, 39, 42]. Finally, the cool-down exercise will include the Ai-Chi method with the focus on respiratory and postural control, through progressive bipodal and unipodal exercises [37, 40, 41]. Individual adaptations will be made based on each participant´'s physical and functional characteristics [37, 43].

The program will be conducted during the “on” phase of dopaminergic medication, approximately 1 h after ingestion. In each session, vital sign collection will take place before and after the immersion [11, 39, 40].

The swimming pool will remain between 32 and 33° Celsius, with a depth of 1.10 m and size 10.75 m long by 2.90 m wide.

The exercises will be instructed by a physiotherapist and three students, all with experience in PD and aquatic physiotherapy.

#### 2.9.4. Control Group

Individuals in the control group will be advised to maintain their usual physical activities for 12 weeks while avoiding high-intensity activities and/or swimming in a heated pool during the study period.

#### 2.9.5. Adverse Outcomes

In order to reduce adverse outcomes each participant will be required to have an accompanying person. The staff will comprise professionals and students and will be trained and responsible for assisting research participants during the transition from the ground to the pool and vice versa, as well as monitoring vital signals (arterial blood pressure, heart rate, respiratory rate, and peripheral saturation of O_2_) before and after immersion. The subjective perception of stress will also be monitored, and in case of discomfort or signs of health risk (dizziness, anxiety, muscle and joint pain, and angina), the training will be interrupted and the participant will receive first aid by the research team before being referred to the emergency care unit, if necessary [40].

#### 2.9.6. Sample Size

Based on the prevalence of individuals with PD in Curitiba, a sample calculation was performed using GPower 3.1. As a result, a sample of 30 individuals will be required, with 15 assigned to the intervention group and 15 assigned to the control group.

### 2.10. Statistical Analysis

The data will be analyzed for sphericity and homogeneity with Shapiro–Wilk test. The ANOVA mixed model will be used to compare pre- and postintervention and intergroup comparisons. Afterward, a Bonferroni post hoc analysis will be performed on variables with statistically significant differences to identify which assessments differ from each other. The statistical power will be *p* > 0.05, and the effect size will also be shown. SPSS 20.0 statistical software will be used in all the analyses.

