## 2. Materials and Methods

### 2.1. Study Design

This is a protocol for a controlled single blinded clinical trial [20].

The project was approved by the Ethics Committee of the Federal University of Paraná under number 39816320.1.0000.0102. The WPEP study protocol was developed based on the recommendations for clinical trial protocols of the Standard Protocol Items: Recommendations for Interventional Trials (SPIRIT) [21]. This is a high-intensity aquatic physical exercise program to be conducted with individuals with a clinical diagnosis of PD, which will be assessed in two phases, prior to the start of the program and after its completion.

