### 2.4. Assessments

All assessments will be performed at the “on” stage of dopaminergic medication, approximately 1 h after intake. The assessment instruments will take place in three stages: Assessment 1 (initial), followed by 12 weeks of intervention or control period; Assessment 2, after the intervention period or control of the study; Assessment 3, after a 4-week follow-up (no intervention).  Figure 1 shows the sequence of evaluations and interventions.

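### The Shapiro–Wilk test is assigned to sphericity and homogeneity, but it tests only normality and cannot detect a failure of either

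*Protocol article*

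**What the plan says.** The statistical section (2.10) opens with the assumption check: "The data will be analyzed for sphericity and homogeneity with Shapiro–Wilk test". It then names the main analysis, "The ANOVA mixed model will be used to compare pre- and postintervention and intergroup comparisons", and the follow-up, in which "a Bonferroni post hoc analysis will be performed on variables with statistically significant differences to identify which assessments differ from each other". It mentions no other assumption test, no correction to the F-tests and no alternative if an assumption fails. Normality, the one property Shapiro–Wilk addresses, is not mentioned.

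The number of time levels is not consistent. Section 2.4 says "The assessment instruments will take place in three stages": baseline, after the 12-week period, and after a further 4 weeks without intervention. Section 2.1 describes a programme "which will be assessed in two phases, prior to the start of the program and after its completion". Section 2.10 itself speaks of pre- and postintervention. Section 2.9.6 gives the size: "a sample of 30 individuals will be required, with 15 assigned to the intervention group and 15 assigned to the control group".

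**The concern.** A mixed ANOVA rests on three separate conditions: normal residuals, equal variances between arms and, with three or more time levels, sphericity (equal variances of all pairwise differences between assessments). Shapiro–Wilk speaks to the first only. A team that follows section 2.10 literally could obtain an unremarkable Shapiro–Wilk result while the two assumptions named in the sentence remain unexamined.

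At stake is the error rate of the time and group-by-time tests, which are too liberal when sphericity fails and no correction is applied. Section 2.4 spaces the assessments unequally (12 weeks, then 4), so a closer correlation between the second and third is plausible. That would make the variances of the differences unequal.

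**Working it through.** The article states no figure for this point, so there is none to reproduce. The check asks whether Shapiro–Wilk reacts to the named assumptions, and what an uncorrected test would cost.

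**Inputs from the article.** 15 per arm (2.9.6), so N = 30; k = 3 assessments (2.4).

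**Assumptions.** Normal data, no treatment effect, and the correlations and SDs shown below. A 5% level is also assumed, because 2.10 writes only "The statistical power will be *p* > 0.05".

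**Group-by-time test.** F = [SS(interaction)/(k − 1)] / [SS(error)/((k − 1)(N − 2))], on 2 and 2 × 28 = 56 degrees of freedom. Greenhouse–Geisser multiplies both by the estimated ε, where ε = tr(A)² / [(k − 1) tr(A²)] and A is the double-centred covariance matrix.

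**Worked ε.** Take unit variances and correlations 0.6 (assessments 1–2), 0.5 (1–3) and 0.9 (2–3).
- The variances of the differences, 2(1 − r), are 0.8, 1.0 and 0.2, which are clearly unequal.
- tr(A) = (0.8 + 1.0 + 0.2)/3 = 0.667 and tr(A²) = 0.338.
- ε = 0.444/(2 × 0.338) = 0.66.
- The corrected degrees of freedom are about 2 × 0.66 = 1.3 and 56 × 0.66 = 37.

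**Simulated type I error, uncorrected test** (20,000 or 40,000 null trials per row; Monte Carlo standard error at most about 0.2 percentage points):

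| Assumed correlations (1–2 / 1–3 / 2–3) | ε | Error |
|---|---|---|
| 0.7 / 0.7 / 0.7 (spherical) | 1.00 | 5.1% |
| 0.8 / 0.75 / 0.85 | 0.92 | 5.4% |
| 0.7 / 0.65 / 0.8 | 0.91 | 5.5% |
| 0.6 / 0.55 / 0.75 | 0.90 | 5.5% |
| 0.5 / 0.4 / 0.8, SD 1.3 after baseline | 0.82 | 6.1% |
| 0.6 / 0.5 / 0.9 | 0.66 | 7.0% |
| 0.5 / 0.5 / 0.9 | 0.65 | 7.3% |
| 0.3 / 0.3 / 0.97 (extreme) | 0.53 | 8.4% |

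With Greenhouse–Geisser the error was 4.9% at ε 0.65, 5.1% at ε 0.53 and about 4.7% under sphericity.

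**Does Shapiro–Wilk notice?** It rejected in 5.1% of trials under sphericity, 3.8% at ε 0.65 and 4.7% at ε 0.53, so it stayed near its nominal level throughout. Mauchly's test flagged the last two scenarios in at least 99% of trials.

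**Homogeneity.** With a 4:1 variance ratio between arms, Shapiro–Wilk rejected in 5.0% of trials and Levene's test in 62%. The F-test held 5.2% at 15/15. It rose to about 10% at an assumed 15/10 with the smaller arm more variable, and Greenhouse–Geisser did not repair this (about 9%).

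**Two time levels.** There is then only one pairwise difference, so ε = 1 by definition; the simulated error was 4.8%.

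**The case against.** The strongest reply is that this is a slip of wording. The paragraph shows intent to examine sphericity and homogeneity, and it contains another evident slip in its sentence on power; the author may have meant normality. That is possible, but it does not rescue the sentence. If normality was meant in place of sphericity, Shapiro–Wilk is still the wrong test for homogeneity. A fuller plan may add corrections, but it would have to replace this rule, not merely supplement it.

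Several stronger readings are tempting and are not supported:

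- **That the F-tests will be run uncorrected.** Section 2.10 does not say so, and it does not make a Shapiro–Wilk result the condition for proceeding. It states no correction, which is less.
- **That sphericity is likely to fail.** The unequal spacing makes failure plausible, but the article gives no correlations. Milder values with the same ordering give only 5.4% to 5.5%.
- **That three time levels are settled.** Section 2.4 and the plan to find which assessments differ favour three; section 2.1 and the pre/post wording favour two.
- **That unequal variances already harm the planned design.** At 15/15 they barely do.
- **That the frequency-domain heart rate variability outcomes add a further fault because they are skewed.** The article says nothing about their distribution, and skewness is a matter of normality, which Shapiro–Wilk does address.

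**Conclusion.** The point holds in a narrow form: the article names a test that cannot detect a failure of either assumption assigned to it. This is an error of statement and does not depend on any unseen document.

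The demonstrable harm is modest. It arises only if three assessments enter the model and no correction is applied. The type I error of the group-by-time test is then about 5.4% to 7%, and about 8% in an extreme case, against an assumed nominal 5%. These figures rest on assumed correlations and normal data.

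The homogeneity part has practical weight only if the arms end up unequal. That is conceivable: the Discussion anticipates difficulty with adherence, and sections 2.2 and 2.9.1 exclude participants whose medication changes. The 15/10 split used to show it is an assumption. The point merits correction before analysis but does not threaten the design.

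**What to change.** Rewrite the opening of section 2.10 so that each assumption has a check that can detect its failure:

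- **Normality:** Shapiro–Wilk, on the model residuals, for this purpose only.
- **Sphericity:** when three assessments are analysed, apply the Greenhouse–Geisser correction by default to the within-subject and interaction tests.
- **Homogeneity of variance:** Levene's test, with a heteroscedasticity-robust or Welch-type comparison if it fails. Levene's test only detects unequal variances; the robust or Welch-type comparison is what deals with them.
- **Time levels:** state how many assessments enter the model, and reconcile sections 2.1, 2.4 and 2.10. If only two enter, drop the reference to sphericity.

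This takes a few sentences, uses standard methods and keeps the planned mixed ANOVA. The statistical price is a very slightly conservative interaction test when sphericity in fact holds, at about 4.6% to 4.7% instead of 5%.
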